After the random allocation, sessions related to the interventions (family-based single dignity intervention and expressive writing) will take place at the time that will be set with caregivers. To avoid sharing experiences between caregivers, we will try to provide a situation that caregivers do not have contact with each other. For this, we will include a maximum of four caregivers in a day from different rooms of the oncology center in Firozgar hospital (study setting) and we will set a specific time for each caregiver so that there is no possibility of contact and sharing experiences with each other. Also, after discharging the four previously included caregivers from the hospital, we will include the other new four caregivers to minimize their contact. On the other hand, recruitment will be stopped until discharging the four previously included caregivers. Caregivers in all intervention groups will receive routine care such as family counseling and meaning therapy, and they will be asked not to participate in other psychotherapy programs. Since the interventions used in the current study are interview-based, we cannot blind the investigators and caregivers to the interventions.

Before the intervention session and 1 week and 2 weeks after the interventions, anticipatory grief will be assessed by a 13-item anticipatory grief scale (AGS-13). The mean of AGE-13 score at baseline and throughout the study will be considered as the main outcome variable. The diagram for Standard Protocol Items: Recommendations for Interventional Trials (SPIRIT) is shown in Fig. 2.

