### Sample size calculation

Considering the type I error of 5% (*α*= 0.05) and type II error of 20% (*β*= 0.20, power = 80%) and anticipatory grief score as the key variable, we manually, without the use of any software, calculated the required sample size using the following formula [36, 37]:
$$ n=\frac{2\left[{\left(\mathrm{a}+\mathrm{b}\right)}^2\times {\upsigma}^2\right]}{{\left({\mu}_1-{\mu}_2\right)}^2} $$

*n* = sample size in each group

*μ*_1_ = mean for anticipatory grief score in group 1 (considered as 78.17 based on the study of Garand et al. [38])

*μ*_2_ = mean for anticipatory grief score in group 2 (considered as 64.49 based on the study of Garand et al. [38])

*σ* = variance (SD) for the mean of anticipatory grief score, which was considered as 23.1 (the average SDs reported for anticipatory grief score in the 2 groups of Garand et al. study [38]).

*a* = conventional multiplier for alpha = 0.05 that was 1.96

*b* = conventional multiplier for power = 0.80 that was 0.842

Overall, based on the formula and given a 10% drop-out in each group, we will need a sample size of 50 caregivers for each intervention group.

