### Statistical analysis for the quantitative phase

All collected data will be coded and then will be entered into the SPSS software version 18 (SPSS, Inc., Chicago, IL, USA) for performing statistical analysis. To ensure the accuracy of the dataset, it will be double-checked by another investigator. The analyses will be performed on the basis of an intention-to-treat (ITT) approach. Therefore, missing values will be treated according to the last-observation-carried-forward method. The Kolmogorov-Smirnov test will be used to examine the normal distribution of quantitative variables. We will normalize the non-normally distributed variables using log transformation. To detect differences in quantitative and categorical variables between the intervention groups, we will use the analysis of variance (ANOVA) and chi-square test, respectively. To determine the effect of family-based dignity intervention and expressive writing on anticipatory grief, we will use repeated measures ANOVA. In this analysis, the intervention groups (family-based dignity intervention, expressive writing, combined intervention, and control groups) will be considered as the between-subjects factor and the time points (before and 1 week and 2 weeks after the interventions) will be considered as the within-subjects factor. Also, to assess differences between the intervention groups in terms of mean changes of anticipatory grief, the multivariate analysis of covariance (ANCOVA) will be applied by considering baseline measurements and variables different between the groups as covariates. *P* value<0.05 will be considered as a significant level.

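### The main outcome wording and the repeated measures ANOVA count the pre-intervention score as a response; if the three-visit mean or the group main effect is tested, only two thirds of a full effect remains

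*Protocol article*

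**What the plan says.** In the protocol article, Study design for the quantitative phase sets three assessments of the anticipatory grief scale: before the intervention session, and 1 and 2 weeks after the interventions. It then defines the outcome: "The mean of AGE-13 score at baseline and throughout the study will be considered as the main outcome variable" (AGE-13 is evidently a slip for AGS-13).

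Statistical analysis for the quantitative phase uses repeated measures ANOVA to determine the effect of the interventions. Group is the between-subjects factor, and "the time points (before and 1 week and 2 weeks after the interventions) will be considered as the within-subjects factor". The section does not say whether the group main effect or the group-by-time term carries the intervention effect. It adds an analysis of covariance "to assess differences between the intervention groups in terms of mean changes of anticipatory grief", with baseline measurements among the covariates.

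Sample size calculation treats the trial as a two-group comparison of one score: means 78.17 and 64.49, SD 23.1, a "conventional multiplier for alpha = 0.05 that was 1.96", and a "conventional multiplier for power = 0.80 that was 0.842". With 10% drop-out this gives 50 per group. Neither repeated measurement nor a correlation between visits enters the formula.

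**The concern.** Baseline is measured before treatment, so under randomisation its expected difference between arms is zero. Averaging it with two follow-up scores adds a zero to the numerator of the treatment comparison. The group main effect of a repeated measures ANOVA is a test on exactly that average, so it inherits the dilution whenever baseline is a level of the time factor.

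The sample size, by contrast, assumes that the full difference is tested. If the result is read from the three-visit mean or the group main effect, an intervention that works as well as the plan supposes could be reported as ineffective more often than the planned one time in five. The other comparisons in the same section do not share this weakness, so the conclusion could depend on which line of the output is read.

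**Working it through.** **Inputs.** From Sample size calculation: difference 78.17 − 64.49 = 13.68; SD 23.1; multipliers 1.96 (two-sided 5%) and 0.842 (80% power); 10% drop-out; 50 per group. From Study design for the quantitative phase: one baseline and two follow-up visits. The correlation r between visits is not given. I assume it equal for all pairs of visits, with equal SDs, and show a range.

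**Reproducing the plan.** n = 2 × (1.96 + 0.842)² × 23.1² / 13.68² = 44.77, so 45 per group; 45 / 0.9 = 50. The stated figure reproduces. With 45 per group, power is 80.2% by the normal approximation and 79% by the t-test. The pairwise powers below use the two-sided t-test.

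**The diluted comparison.** With no effect at baseline and the full effect at both follow-ups, the expected difference in the three-visit mean is (0 + 13.68 + 13.68)/3 = 9.12, which is 2/3 of 13.68. The SD of that mean is 23.1 × √((1 + 2r)/3). At r = 0.5 it is 23.1 × √(2/3) = 18.86, so the standardised difference is 9.12/18.86 = 0.484, against 13.68/23.1 = 0.592 in the plan.

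**Break-even correlation.** Averaging also reduces noise, so dilution does not always cost power. The two effects balance when (2/3)² = (1 + 2r)/3, that is 1 + 2r = 4/3, so r = 1/6. Above that, the three-visit mean is weaker than the single score the plan was sized on; below it, stronger.

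**The undiluted comparisons**, each with the full 13.68:
- Mean of the follow-ups minus baseline (the contrast within group-by-time): SD 23.1 × √(1.5(1 − r)).
- Baseline-adjusted ANCOVA, mean of the two follow-ups: SD 23.1 × √((1 + r)/2 − r²).
- Baseline-adjusted ANCOVA, week 2 only: SD 23.1 × √(1 − r²).

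**Power with 45 evaluable per arm, two arms compared:**

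| r (assumed) | Three-visit mean / group main effect | Post minus baseline | ANCOVA, mean of follow-ups | ANCOVA, week 2 |
|---|---|---|---|---|
| 0 | 89% | 62% | 98% | 79% |
| 1/6 | 79% | 70% | 96% | 80% |
| 0.3 | 72% | 77% | 96% | 83% |
| 0.5 | 62% | 89% | 98% | 89% |
| 0.7 | 54% | about 99% | above 99% | 97% |
| 0.8 | 51% | above 99% | above 99% | above 99% |

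The ANCOVA variance (1 + r)/2 − r² is largest at r = 0.25, so 96% is close to its floor.

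**Four-arm check.** With one arm differing by 13.68 from three equal arms, the overall F test for the group main effect (3 df) has 74.4%, 63.7% and 55.0% power at r = 0.3, 0.5 and 0.7. The group-by-time F test (6 df) has 69.7%, 85.7% and 98.3%. The loss is therefore not an artefact of comparing two arms at a time.

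**Sample size equivalent.** By the normal approximation, restoring 80% power for the three-visit mean would take 68 evaluable (76 recruited) per arm at r = 0.5, or 81 (90) at r = 0.7, against the planned 50.

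**The case against.** A reader might infer that the trial's tested effect is cut to two thirds and that its power is below 80%. The article does not support that, for four reasons.

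- It never names the group main effect as the test. In a model with a pre-intervention level, group-by-time is the term that expresses an intervention effect, and it is not diluted. This stands. At low correlation, though, that term is itself short of 80%: 77% pairwise and 69.7% for the four-arm F test at r = 0.3.
- The outcome sentence directly follows the list of three assessments and can be read as the mean score at each visit. No listed analysis explicitly takes a pooled three-visit mean as its response. This stands as a possible reading, but baseline is then still part of the main outcome and still a response level in the ANOVA.
- An analysis with baseline as covariate is already planned and exceeds 80% on the plan's inputs over the range shown, apart from week 2 alone at correlations near zero, where it matches the plan's own 79%. This stands, and it is why the remedy costs so little.
- The shortfall depends on a correlation above about 1/6, which the article does not give. This stands. A value that low would be surprising for one scale given to the same people one or two weeks apart, but that is a judgement.

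A condensed article may also leave the choice of decisive test to a fuller document. That silence is not the point here. The point is what the article does state: an outcome that includes baseline, and a model that treats baseline as a response.

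**Conclusion.** The point holds conditionally. The main outcome wording takes in a score that treatment cannot affect, and the repeated measures ANOVA treats that score as a response. If the three-visit mean or the group main effect is what gets tested, 2/3 of the effect remains, and power is about 72% to 51% for correlations of 0.3 to 0.8. If another planned comparison decides, this loss does not arise.

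The 2/3 assumes a full effect at both follow-ups; an effect at only one of them would leave 1/3. The power figures assume equal correlations and SDs across visits, 45 evaluable per arm, and the plan's standardised difference of 0.592. They take 13.68 and 23.1 at face value; whether those inputs suit a scale running from 13 to 65 is a separate question. The outcome should be reworded before results are seen, but nothing here shows that the trial as a whole is underpowered.

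**What to change.** 1. In Study design for the quantitative phase, define the main outcome on post-intervention AGS-13 only, with baseline AGS-13 as a covariate and not as part of the outcome.
2. In Statistical analysis for the quantitative phase, make the already planned baseline-adjusted ANCOVA the single primary analysis, on one prespecified response: the mean of the 1- and 2-week scores, or the 2-week score if the sponsor prefers one time point. The mean has the higher power on these inputs (98% against 89% at r = 0.5). Either is sound, but only one should be named.
3. Keep the repeated measures ANOVA as supportive, and state that only its group-by-time term, not the group main effect, will be read as evidence of an intervention effect.

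The cost is a few sentences. No new data, visits or participants are needed.

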**Fig. 2 Fig2:**
[figure not shown]
Standard Protocol Items: Recommendations for Interventional Trials (SPIRIT) chart of the enrolments and assessments during randomized controlled trials. The “*X*” refers to what is done in the given period. Abbreviations: WK week

### Sample size calculation

Considering the type I error of 5% (*α*= 0.05) and type II error of 20% (*β*= 0.20, power = 80%) and anticipatory grief score as the key variable, we manually, without the use of any software, calculated the required sample size using the following formula [36, 37]:
$$ n=\frac{2\left[{\left(\mathrm{a}+\mathrm{b}\right)}^2\times {\upsigma}^2\right]}{{\left({\mu}_1-{\mu}_2\right)}^2} $$

*n* = sample size in each group

*μ*_1_ = mean for anticipatory grief score in group 1 (considered as 78.17 based on the study of Garand et al. [38])

*μ*_2_ = mean for anticipatory grief score in group 2 (considered as 64.49 based on the study of Garand et al. [38])

*σ* = variance (SD) for the mean of anticipatory grief score, which was considered as 23.1 (the average SDs reported for anticipatory grief score in the 2 groups of Garand et al. study [38]).

*a* = conventional multiplier for alpha = 0.05 that was 1.96

*b* = conventional multiplier for power = 0.80 that was 0.842

Overall, based on the formula and given a 10% drop-out in each group, we will need a sample size of 50 caregivers for each intervention group.

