### Post-trial care

After finishing this study, we will recommend caregivers to receive routine care such as family counseling and meaningful therapy for having good mental health. Also, at the end of the study, we will assess whether combined interventions of family-based dignity and expressive writing or each intervention alone reduce anticipatory grief by 10 points, based on the AGS-13, compared to the routine care as a control intervention. The 10-point decrease or increase is considered a clinically and statistically significant change in anticipatory grief based on the study of Garand et al. [38] and also given the total AGS-13 scores ranging between 13 and 65.

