### Anticipatory grief scale

The original form of anticipatory grief scale was designed by Theut et al. to assess anticipatory grief in spouses of Alzheimer’s patients [41]. This form consisted of 27 items measuring anticipatory grief on a Likert scale, ranging from 1 (strongly disagree) to 5 (strongly agree). The items should be summed into a total score ranging from 27 to 135 with a higher score indicating higher levels of anticipatory grief. However, 8 items (2, 5, 8, 11, 19, 22, 26, and 27) have a positive bearing and therefore must be reversed before the total score is calculated. In addition to the total score of anticipatory grief, the score of seven subscales including anger, guilt, anxiety, irritability, sadness, feelings of loss, and decreased ability to function in performing usual tasks can be reached from this scale. In 2019, Holm et al. [42] introduced a short form of AGS containing 13 items and was named AGS-13 (items 1, 3, 4, 7, 10, 15, 16, 18, 20, 21, 23, 24, and 25 of the original form). This scale specifically measures a total score of anticipatory grief in family caregivers of cancer patients and also consists of two subscales, named “Behavioral reactions” and “Emotional reactions,” which capture the behavioral and emotional reactions of grief in caregivers participating in palliative care. To obtain a total score of anticipatory grief in AGS-13, like the original form, the items should be summed into a total score ranging between 13 and 65. Higher scores indicate higher anticipatory grief in caregivers of cancer patients. No item should be reversed before calculating the total score. To increase the data quality obtained from the AGS-13, investigators will give a brief explanation about the questionnaire and its items to participants. Also, we have no concern about the effect of baseline AGE-13 responses on the second and third assessments (1 week and 2 weeks after the interventions) because Holm et al. reported that the questionnaire has sufficient sensitivity that means any true changes in anticipatory grief result in a change in the total score of AGS-13 [42].

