### Strengths

This is the first mixed-methods study investigating the effects of family-based dignity intervention and expressive writing on anticipatory grief in family caregivers of dying cancer patients through mixing quantitative and qualitative assessments. Also, it should be noted that the interventions are of low cost and can easily be carried out in palliative care centers. In this study, caregivers are assigned to four groups using block randomization. The sample size of this study is adequate and provides sufficient power to detect the efficacy of interventions. In addition to the effects of family-based dignity intervention and expressive writing alone, the combined effects of these interventions are examined in a separate intervention group.

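### The sample size rests on means and an SD that together cannot occur on the AGS-13, so the stated 80% power is not established for the trial's endpoint

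*Protocol article*

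**What the plan says.** All places are in the protocol article.

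- **Sample size calculation.** The section gives the "mean for anticipatory grief score in group 1 (considered as 78.17", 64.49 for the second group and an SD of 23.1, all from one cited study. The error rates are 5% and 20%, with multipliers 1.96 and 0.842. After 10% drop-out it arrives at 50 caregivers per arm.
- **Study design for the quantitative phase.** The main outcome is the score on the 13-item scale, measured at baseline and 1 and 2 weeks after the interventions.
- **Anticipatory grief scale.** For the AGS-13, "the items should be summed into a total score ranging between 13 and 65". For the original 27-item form, "The items should be summed into a total score ranging from 27 to 135".
- **Post-trial care.** The trial will assess whether each intervention lowers the AGS-13 score by 10 points against routine care. "The 10-point decrease or increase is considered a clinically and statistically significant change in anticipatory grief", with support from the same cited study and from the 13–65 range.
- **Strengths.** "The sample size of this study is adequate and provides sufficient power to detect the efficacy of interventions".

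**The concern.** The planning means and SD are presented as values of the outcome, yet one mean lies off the scale on which the outcome is measured. No section rescales them. The difference behind the calculation (13.68) and the difference to be assessed (10) are also not linked, although both refer to the same source study.

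This calculation is the only support for the 80% power and for the claim under Strengths. If its inputs belong to another scale, a reader cannot tell from the plan what difference on the AGS-13 the 200 caregivers can detect, or with what power. In addition, no fixed number of points can be statistically significant in advance: that depends on the observed spread and the number analysed.

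**Working it through.** **1. The plan's own figure.** Inputs from the sample size section: means 78.17 and 64.49, SD 23.1, multipliers 1.96 and 0.842, drop-out 10%.

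- Difference: 78.17 − 64.49 = 13.68; standardised, 13.68/23.1 = 0.592.
- n = 2 × (1.96 + 0.842)² × 23.1² / 13.68² = 44.77, so 45 evaluable per arm.
- Drop-out: 45/0.9 = 50 per arm, 200 in total.

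The figure reproduces.

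**2. Do the inputs fit a 13–65 scale?** On a scale from *L* to *U*, the largest possible SD at mean *m* is √[(U − m)(m − L)].

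- Mean 78.17: above the maximum by 78.17 − 65 = 13.17. Impossible.
- Mean 64.49: largest SD = √(0.51 × 51.49) = 5.12. It cannot go with an SD of 23.1.
- SD 23.1: the largest SD at any mean is 26 (at 39). Solving (65 − m)(m − 13) ≥ 23.1² gives means from about 27.1 to 50.9 only, which includes neither planning mean.

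All three values are possible on a 27–135 scale.

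**3. What rescaling would give (assumption: the source used the 27-item form).** The factor is (65 − 13)/(135 − 27) = 52/108 = 0.4815. The means become 37.6 and 31.1, the difference 6.59 and the SD 11.1. The ratio stays 0.592, so n stays 45, but the 80% power then belongs to 6.59 AGS-13 points.

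**4. Power for 10 AGS-13 points with 45 evaluable per arm.** Two-sample t test, two-sided 5%, two arms compared as in the plan's formula. The SDs are assumptions, because the documents give none for the AGS-13. The n needed is 2 × 2.802² × SD²/10², rounded up, then divided by 0.9 and rounded up.

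| Assumed SD | Power for 10 points | n per arm for 80%, evaluable | After 10% drop-out |
|---|---|---|---|
| 11.12 | 99% | 20 | 23 |
| 12 | 97% | 23 | 26 |
| 15 | 88% | 36 | 40 |
| 17 | 79% | 46 | 52 |
| 20 | 65% | 63 | 70 |

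Power is 80% at an SD of about 16.8 (16.7 by the t test, 16.9 by the normal approximation). For comparison, scores spread evenly over 13–65 would have an SD of 52/√12 = 15.0.

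**5. Detectable difference.** With 45 evaluable per arm and 80% power it is about 0.60 SD: 0.597 × 11 = 6.6 points and 0.597 × 12 = 7.2 points.

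**The case against.** The strongest reply is that the formula depends only on difference divided by SD, and this ratio does not change under linear rescaling. If the source figures are simply on the longer form, 45 per arm remains the answer and 10 points has about 99% power. The baseline-adjusted analysis in the statistical section would normally need fewer participants still. The fault would then lie in the justification and not in the size of the trial. This stands, as far as the assumption about the form stands, and it limits the conclusion.

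Four stronger readings are tempting and are not supported:

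- **The trial is underpowered.** Pairing 10 points with SD 23.1 gives about 53% power and a need for 84 evaluable per arm. But 23.1 is one of the values that do not fit this scale alongside the stated means, so this is not a realistic scenario. Power falls below 80% only if scores are spread more widely than an even spread over the whole scale.
- **Each input is impossible.** Only 78.17 is impossible by itself. For 64.49 and 23.1 it is the pairing that fails.
- **The source study used the 27-item form.** The ranges suggest it, but the documents do not say so.
- **Ten points is the formal success rule and ignores the AGS-13 range.** The plan says only that it will assess a 10-point reduction, it cites the 13–65 range in support, and it tests at P < 0.05. A result that is significant yet below a clinical threshold is not a defect, nor is sizing for a difference other than that threshold.

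**Conclusion.** The point holds. The stated means and SD cannot describe the AGS-13, and the planned 13.68 is not the 10 points to be assessed. The 80% power and the statement under Strengths are therefore not established for this endpoint. The arithmetic itself is correct.

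The documents do not show that 50 per arm is too few. That depends on the AGS-13 SD, which they do not give: 10 points is well covered at an SD of 11–12 or 15 and falls short of 80% above about 16.8. These figures assume 45 evaluable per arm and an unadjusted two-arm comparison at two-sided 5%; the SD of 11.1 assumes in addition that the source used the 27-item form.

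The description of 10 points as statistically significant is a separate, smaller error of wording. Correction is needed because this is the trial's only sample size justification.

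**What to change.** - **Sample size calculation:** restate it on the 13–65 scale with an assumed AGS-13 SD, its source, and the 10-point difference. If the cited study used the 27-item form, say so and show the rescaling.
- **Same section:** for the planned 50 per arm, report the detectable difference (about 0.60 SD with 45 evaluable, or 6.6–7.2 points at SD 11–12) and the power for 10 points over a range of SDs that extends beyond 17.
- **Test-retest sample:** the 30 caregivers already planned can serve as a rough check of the SD only. With 29 degrees of freedom the 95% limits are about 0.80 to 1.34 times the estimate.
- **Post-trial care:** remove the reference to statistical significance from the 10-point statement and keep 10 points as a clinical threshold only.
- **Strengths:** align the claim of sufficient power with the restated calculation.

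The cost is a text amendment, with no extra participants or measurements. If the AGS-13 SD proves to be above about 17, the restated text should say that power for 10 points is below 80%.

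### The 80% power belongs to one unadjusted two-arm comparison, not to the planned four-group repeated measures ANOVA, so the claim of sufficient power is too broad

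*Protocol article*

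**What the plan says.** All references are to the protocol article.

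- *Sample size calculation* uses n = 2(a+b)²σ²/(μ₁−μ₂)². The inputs are a "conventional multiplier for alpha = 0.05 that was 1.96", a "conventional multiplier for power = 0.80 that was 0.842", the "mean for anticipatory grief score in group 1 (considered as 78.17 based on the study" it cites, the "mean for anticipatory grief score in group 2 (considered as 64.49 based on the study" it cites, and an SD "for the mean of anticipatory grief score, which was considered as 23.1". With an allowance "given a 10% drop-out in each group", it arrives at 50 per group. The section does not mention a four-group test, multiple comparisons or repeated measures.
- *Statistical analysis for the quantitative phase*: "To determine the effect of family-based dignity intervention and expressive writing on anticipatory grief, we will use repeated measures ANOVA". Group has four levels and time has three (before, 1 week, 2 weeks). A baseline-adjusted ANCOVA on changes is also planned.
- *Study design for the quantitative phase* makes the mean score at baseline and over the study the main outcome.
- *Introduction* aims to compare the interventions with each other as well as with routine care.
- *Post-trial care* sets one 10-point target against routine care, both for the combination and for each intervention alone.
- *Strengths*: "The sample size of this study is adequate and provides sufficient power to detect the efficacy of interventions".

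**The concern.** A power figure is a property of a particular test. Here the figure comes from a two-arm comparison, the conclusion is to come from a four-group analysis with three time points, and the adequacy claim covers the interventions as a whole. No contrast is named to which the 80% could attach. If the planned test has materially less power than stated, a non-significant overall result in a trial described as adequately sized could be misread as evidence that the interventions do not work.

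**Working it through.** **1. The plan's own figure.** Difference 78.17 − 64.49 = 13.68; SD 23.1; d = 13.68/23.1 = 0.592.
n = 2 × (1.96 + 0.842)² × 23.1² / 13.68² = 44.77, so 45. With 10% drop-out, 45/0.9 = 50. The stated 50 per group reproduces.

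**2. What that figure buys.** For a two-sample t-test the noncentrality is d/√(2/n). With n = 45 it is 0.592/√(2/45) = 2.81, giving 79% power (80% by the normal approximation). With n = 50 it is 2.96, giving 83%.

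**3. Several pairwise comparisons.** Same difference, 45 per arm, Bonferroni, t-test: 64% for three comparisons (α = 0.05/3) and 55% for all six (α = 0.05/6).

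**4. One-way four-group F-test on a single score.** λ = n Σ(μᵢ − μ̄)²/σ², with 3 and 4(n − 1) df. At n = 45, n d² = 45 × 0.3507 = 15.78.

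| Arm effects (control, single, single, combined) | Σ(μᵢ − μ̄)² | λ, n = 45 | Power, n = 45 | Power, n = 50 |
|---|---|---|---|---|
| 0, d/2, d/2, d | d²/2 | 7.89 | 64% | 69% |
| 0, d, d, d | 3d²/4 | 11.84 | 83% | 87% |
| 0, d, d, 2d | 2d² | 31.56 | 99.9% | over 99.9% |

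For a fixed largest difference d, the sum of squares is smallest when the two middle arms lie at the midpoint, so the first row is the least favourable pattern. A simulation of that row (20,000 runs, n = 45) gave 63%.

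**5. Three time points.** Power now depends on the within-person correlation ρ, which the document does not give. Assume compound symmetry, ρ = 0.3 to 0.8, equal baselines, the full effect at both later visits, and 45 per arm.

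- *Group main effect averaged over all three times.* The arm difference shrinks to 2/3 and the variance becomes σ²(1 + 2ρ)/3, so λ is multiplied by 4/[3(1 + 2ρ)]: 0.833 at ρ = 0.3 and 0.513 at ρ = 0.8. Least favourable pattern: λ 6.58 to 4.05, power 55% down to 36%. Equal effects: λ 9.86 to 6.07, power 74% down to 51%.
- *Group-by-time interaction.* λ is multiplied by (2/3)/(1 − ρ), with 6 and 352 df. Least favourable pattern: λ 7.52 to 26.30, power 49% to 98%.
- *ANCOVA on one post-intervention score, 3-df group test.* λ is divided by 1 − ρ². Least favourable pattern: λ 8.67 to 21.92, power 68% to 98% (77% at ρ = 0.5).

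**The case against.** Sizing a multi-arm trial on one pairwise difference is common, and here the arithmetic is right. Moving to a four-group test does not in itself push power below 80%. *Post-trial care* applies the same target to the combination and to each intervention alone; the closest pattern is equal effects, where the one-way F-test has 83%. Baseline adjustment or the interaction test can exceed 90% if scores are well correlated over time. All of this stands.

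It also rules out two stronger readings. A reader might infer that the planned test has 64% power because the two interventions add up. Additivity does not give that figure: if each single intervention gives d and the combination 2d, power is 99.9%. The 64% also needs 13.68 to be the combined effect with each single effect exactly half of it, and no section says so. It is also for a one-way test of one score, which is not the planned analysis. A reader might further infer that 50 per group is too few. That would require an effect pattern and a correlation that the document does not give.

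What the objection does not answer is that the 80% was never computed for the test that is to determine the effect, while *Strengths* states adequacy without that limit.

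**Conclusion.** The point holds as a mismatch between the stated power and the planned test; it does not show that the trial is underpowered. The 80% describes one pairwise difference of 13.68 at unadjusted 5%. Power for the planned analysis depends on which term of the repeated measures ANOVA is read, on the pattern of effects and on the correlation. The clearest risk is the group main effect: with baseline averaged in, it falls short of 80% under both the least favourable and the equal-effects pattern across the assumed range. The wording of the main outcome, which includes baseline, leaves that reading open.

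Every figure is conditional on the plan's d of 0.592. The source mean of 78.17 lies above the AGS-13 maximum of 65, so neither the 80% nor the alternatives computed here may carry over to the outcome as it will be measured.

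**What to change.** 1. In *Sample size calculation*, state that the 80% applies to a single unadjusted pairwise comparison, and name that contrast.
2. In *Strengths*, limit the adequacy claim to that comparison.
3. In *Statistical analysis for the quantitative phase*, base the effect conclusion on baseline-adjusted pairwise contrasts against control from the ANCOVA already planned, rather than on an overall F or on a main effect that averages in baseline.
4. If the overall test stays primary, give its power as a range, with the assumed effect pattern and correlation beside it.

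This takes a few sentences and no extra caregivers. The cost is that comparisons not named, including those between interventions that the *Introduction* sets as an aim, become secondary or carry a stated power below 80%. Which contrast to name is the investigators' choice; the document does not settle it.
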